## Background

Dental caries (tooth decay) remains the most prevalent chronic disease of childhood, even ahead of asthma and hay fever [1]. According to the Child Dental Health Survey 2010, the proportion of Australian children with caries experience (decayed, missing and filled teeth ‘dmft + DMFT’ > 0) varied from 48% for children aged 5 years to 69% for children aged 9 years [2]. There is a significant social gradient between socioeconomic status and the prevalence and severity of oral diseases which highlights oral health inequalities and inadequate funding for prevention and treatment [3]. Dental caries is an entirely preventable dynamic disease, with an interplay of risk factors that protect against or cause progression of the disease. In general diet, oral hygiene and fluoride exposure are the most common factors assessed when determining an individual’s risk level for the disease [4].

If dental caries remains untreated, it can have serious consequences that require costly treatment. Dental caries can lead to physical and psychosocial consequences including pain, sepsis, and disturbed eating, drinking and sleep pattern [3]. Poor oral health can have a significant impact on a child’s development including below average height, weight, and head circumference, and absenteeism from school [5, 6]. The demand for dental care is increasing and with it the total costs. Recurrent expenditure on dental care services in Australia increased from $6.6 billion AUD in 2006–07 to $10.2 billion AUD in 2016–17 (adjusted for inflation), at an average annual growth rate of 4.4% [7]. Dental extractions and restorations are the most common reported causes for hospital admission among Australian children [8]. For instance, between 2000 and 2009, a total of 43,937 children (0–14 years) were hospitalised due to various oral conditions in Western Australia (WA) with total costs of $92 million AUD [9].

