The proposed project builds on previous validation trials that examined the feasibility of the teledentistry approach to dental screening [25–27]. The findings showed that the use of dental photography in dental screening is feasible and offered a moderate diagnostic accuracy relative to visual dental screening. Recent systematic reviews indicated that most reviewed studies concerned with teledental diagnosis demonstrated comparable results between photographic and visual inspection techniques [28, 29]. Although telehealth applications are becoming increasingly popular in dentistry, controlled assessments of clinical outcomes, long-term use and economic analyses of teledentistry are still limited [30–32]. A comparison of the costs of teledentistry and its alternatives is of great importance to those making future decisions about implementing a new service. In this study, we propose a paradigm shift in the existing dental services through role substitution and taking advantage of user-friendly mobile technology and the widely available Internet to improve school children access to dental services.

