#### Objectives

To determine the efficacy of a novel teledental pathway of dental care in improving oral health outcomes of school children relative to the usual pathway of dental care. *Hypothesis: The teledental pathway of dental care would be as effective as a routine pathway of dental care in improving children’s oral health.*To compare the costs of the teledental and usual pathway of dental care in school children, from a health system perspective. *Hypothesis: The teledental pathway of dental care would be cost-saving relative to the usual pathway of dental care.*To assess the diagnostic performance of dental screening on the basis of dental images relative to the reference visual dental inspection at the baseline. *Hypothesis: The photographic dental assessment will be as accurate and reliable as the standard visual dental screening.*

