#### Follow up

At 9 months following the baseline dental assessments, all participants will be invited to undergo a standard visual dental check-up to assess the dental status, determine if treatment was received and see whether parents adhere to the recommendations received at the baseline.

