### Outcome assessment

*Primary outcomes* include decay experience in either dentition as measured by the DFT/dft (decay, filled teeth) index at the baseline and 9-month follow up. Teeth will be classified as carious if have arrested caries, caries into dentine or enamel level caries. In addition to the proportion of children becomes caries-active at the 9-month follow-up which refers to the percentage of children developing one or more new caries in any of the previously caries-free teeth when assessed at the baseline. Data will be collected from one of our system’s functional components running on the backend to automatically record dental assessments based on dental images and through the oral health assessment forms completed by OHTs in the control group.

*Secondary outcomes* include the diagnostic performance of photographic dental assessment versus standard dental examination at the baseline. The participants’ dental care utilisation patterns collected via a baseline survey (Additional file 2) and adapted from Kopycka-Kedzierawski et al. [36]. Also, costs comparison between the two pathways of dental care will be conducted to identify the least costly alternative. The resources for the usual pathway of dental care will include vehicle costs, admin costs (e.g. telephone appointments, printing services and postage) and costs of consumables used in visual dental screening and the dental practitioner’s time. The resources for the teledental pathway of dental care include: software licence fees, ICT equipment, Internet and software engineer’s time, admin costs (e.g. telephone appointments, printing services and postage), costs of consumables used in dental photography, tele-assistants (photographer) time, and offsite dental practitioners’ time for reviewing dental images. Dental care costs for all children include the following: restorations, restorations with crowns and extractions. The costing data will be based on those incurred by the health system and will be derived from a survey and web-based open-access sources [37].

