### Data analysis

The sensitivity and specificity values for the photographic caries assessment will be estimated and compared to the reference visual dental assessment at the baseline. Kappa statistic will be used to estimate the inter-rater reliability of the photographic dental assessments by two independent OHTs. 15% of dental images will be re-examined to test intra-rater reliability at least, 4 weeks after the initial review of images.

The baseline data will be used to generate descriptive statistics for the intervention and control groups (teledental versus usual care pathway). General linear regression models will be performed to compare the efficacy of the interventions on decay (mean DFT/dft) between intervention and control groups, adjusting for baseline data collected via a survey that includes tooth brushing (yes/no; frequency); dental visit patterns over the past year, child age, Indigenous status, Socio-Economic Indexes for Areas (SEIFA), private insurance status and educational level of parents. The measure of intervention efficacy will be the difference between the intervention and control groups in adjusted DFT/dft (caries incidence) per child. All analyses will be performed using SAS (version 9.4). In addition, a cost minimisation analysis will be undertaken to compare the costs associated with teledental versus the usual pathway of dental care over 9 months. This will include both the cost of the initial screening, and any subsequent interventions occurring over the 9 months. The analysis will be conducted from the perspective of the health system and, will not take into consideration the costs incurred by the families. All salaries used in the calculation will be based on Australian government rates and will include on-costs.

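### The 9-month cost minimisation counts only delivered treatment, so non-urgent decay that a pathway misses and leaves untreated appears as a saving

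*Protocol article*

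**What the plan says.** The second objective carries the hypothesis "The teledental pathway of dental care would be cost-saving relative to the usual pathway of dental care". Under Data analysis, "a cost minimisation analysis will be undertaken to compare the costs associated with teledental versus the usual pathway of dental care over 9 months". The content of the cost total is then fixed: "This will include both the cost of the initial screening, and any subsequent interventions occurring over the 9 months".

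Outcome assessment lists the treatment items: "Dental care costs for all children include the following: restorations, restorations with crowns and extractions". It gives the purpose as a "costs comparison between the two pathways of dental care will be conducted to identify the least costly alternative". Neither section assigns a cost to decay that is present but untreated when the 9 months end.

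Three other parts of the article bear on the point:

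- **Source of the advice.** Control families receive results from the visual examination, and teledental families receive results from the images (Visual dental examination; Photographic dental assessment). The Abstract adds that every child first has a standard examination to pick out urgent referrals.
- **Accuracy.** Background reports that in previous validation work dental photography "offered a moderate diagnostic accuracy relative to visual dental screening".
- **Follow-up.** At 9 months all children are invited to "undergo a standard visual dental check-up to assess the dental status, determine if treatment was received".

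**The concern.** A cost minimisation compares costs on the footing that outcomes are equivalent. Here the cost side counts treatment that was given and is silent on treatment still owed. A pathway that finds less non-urgent decay will generate fewer restorations, crowns and extractions inside the window and will look cheaper for that reason alone. The article itself warns: "If dental caries remains untreated, it can have serious consequences that require costly treatment". Part of an apparent saving could therefore be treatment put off beyond month 9.

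The primary outcome does not expose this. DFT/dft adds decayed and filled teeth, so it does not separate disease that was managed from disease that was left. The arms could agree on DFT/dft and differ in untreated decay, and the trial could report equal outcome at lower cost. The likely direction matches the stated cost hypothesis, and economic benefit is part of the trial's declared aim.

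**Working it through.** **1. The rule applied to two children.** Each has one carious, non-urgent tooth at baseline that would need a restoration.

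| | DFT/dft at month 9 | Cost counted |
|---|---|---|
| Decay found and filled | 1 (filled) | screening + one restoration |
| Decay missed, untreated | 1 (decayed) | screening only |

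The outcome is the same, and the recorded costs differ by one restoration. This follows from the stated window and item list without any numerical assumption.

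**2. Direction.** The visual examination is the reference standard for the photographs (Objectives; Data analysis), and it also drives the advice in the control arm. Disease missed relative to that reference therefore arises in the teledental arm.

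**3. The plan's own figures.** Inputs from Sample size calculation: 95% confidence, margin 0.1, proportion 0.90, caries prevalence 35%, dropout 20%.

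- n with caries = 1.96² × 0.90 × 0.10 / 0.1² = 34.57, rounded up to 35
- total = 35 / 0.35 = 100, of whom 65 are without caries
- after dropout = 100 / (1 − 0.20) = 125 per group

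These reproduce. The point does not depend on them; they only set the scale below.

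**4. Upper-bound illustration.** Carious children per arm = 125 × 0.35 = 43.75. Missed children = 43.75 × (1 − Se), where Se is photographic sensitivity relative to the visual examination. All Se values are assumptions. The first uptake column assumes that every carious child would need, and would receive, a costed procedure if detected.

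| Assumed Se | Missed children, full uptake | At an assumed 50% uptake | Share of treatment cost for true caries not counted |
|---|---|---|---|
| 0.90 | 43.75 × 0.10 = 4.4 | 2.2 | 10% |
| 0.75 | 43.75 × 0.25 = 10.9 | 5.5 | 25% |
| 0.60 | 43.75 × 0.40 = 17.5 | 8.75 | 40% |

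The last column equals 1 − Se. It does not change with uptake, provided uptake is the same in both arms and missed decay is not treated by another route within 9 months.

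**5. What cannot be computed.** The net cost difference also needs unit costs, uptake, the number of urgent cases removed by the baseline examination, the share of carious children who need a costed procedure, and the cost of false-positive photographs. The article gives none of these.

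**The case against.** Much of the case on the other side stands.

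- **The counts are upper bounds.** Outcome assessment classes arrested and enamel-level lesions as carious, and the visual examination section makes referral depend on severity and urgency. Some carious children would incur none of the costed items even if detected.
- **The 0.90 is not called a sensitivity.** The sample size section calls it only an expected observed proportion. Its use as a sensitivity above is an assumption, as are 0.75 and 0.60.
- **There is a partial safeguard.** Urgent cases should be identified in both arms at baseline, so the point concerns mainly non-urgent decay.
- **Other flows exist.** Decay found by another route and treated in time is counted. Care that follows a false-positive photograph raises teledental cost. Screening, staff, software and vehicle costs also enter the total.
- **The horizon is a legitimate choice.** A window equal to follow-up is openly stated, and baseline sensitivity will be reported in the same trial.

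A reader might infer that poorer photographs always enlarge the teledental saving, or that the plan will yield a false claim of saving. The documents do not support either. False positives pull the other way, and without unit costs nothing shows that the effect would change which pathway is cheaper.

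The objection does not remove the mechanism. False-positive cost is a separate error and does not put a price on missed need. Reporting sensitivity elsewhere leaves the cost comparison itself unchanged.

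**Conclusion.** The point holds as a structural weakness of the cost comparison. With the window and items as written, non-urgent decay that is missed and left untreated costs nothing, and DFT/dft cannot show that outcomes are equal in the sense a cost minimisation needs. The likely direction favours teledental.

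The net size is unknown. The figure of about 4 to 18 children per 125 is a ceiling that rests on assumed sensitivities of 0.90 to 0.60, full uptake, a costed procedure for every carious child, no removal of urgent cases and no treatment by another route. At 50% uptake it becomes about 2 to 9.

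It might also be inferred that the delivered-only comparison is invalid and must be replaced. That goes too far: it is a fair description of spending over 9 months. What it cannot support alone is a statement that teledental saves money.

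**What to change.** Keep the delivered-only cost over 9 months. Add one pre-specified analysis, identical in both arms:

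- At the 9-month visual examination, count untreated decayed teeth judged to need one of the procedures already costed. For this costing, exclude arrested and enamel-only lesions.
- Multiply by the unit costs already used for restorations, crowns and extractions, and add the result to the delivered cost.
- Show untreated decay per arm beside both cost totals.
- Describe teledental as cost-saving only if the saving persists when outstanding need is included.

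No new visit is required, and the article states that data were still being collected. There are costs:

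- A treatment type has to be assumed for each outstanding tooth. The article does not say that treatment need is recorded per tooth, so the form may need an extra item.
- Need is unobserved for children without a 9-month examination. At the planned 20% dropout that is 0.20 × 125 = 25 per arm, and the handling of these children must be stated.
- The added cost also covers new lesions and decay that was reported but not acted on, so it measures outstanding need and does not isolate missed disease.
- The saving shown may be smaller.

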**Methods/design:**

We describe an ongoing parallel, two-armed, non-inferiority randomised controlled trial that compares routine and teledental pathway of dental care in children aged 4–15 years (*n* = 250). Participating schools in Western Australia will be randomly assigned to the control or teledental group, approximately three schools in each group with a maximum of 45 children in each school. All participants will first receive a standard dental examination to identify those who require urgent referrals and then their teeth will be photographed using a smartphone camera. At the baseline, children in the control group will receive screening results and advice on the pathway of dental care based on the visual dental screening while children in the teledental group will receive screening results based on the assessment of dental images. At 9 months follow-up, all participants will undergo a final visual dental screening. The primary outcomes include decay experience and proportion of children become caries active. The secondary outcomes include the diagnostic performance of photographic dental assessment and costs comparison of two pathways of dental care.

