#### Visual dental examination

A standard dental screening (without radiography) will be performed by registered OHTs (operators) who are blinded to the group allocation of the school. Head-mounted lighting, disposable mirrors and probes will be used to conduct the visual dental screening. Findings from the visual dental assessment will be recorded on an oral health assessment form that follows the guidelines for oral health surveys developed by the WHO [35]. Following the completion of the baseline dental screening, parents of school children allocated to the control group will receive a copy of the screening results based on the visual inspection performed by onsite OHTs. Based on the severity and urgency of dental conditions, children with active caries will be referred to local dental providers for further investigations. Children who are screened caries-free or at low-risk, will not receive active treatment other than OHP leaflets.

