### Sample size calculation

The sample size calculation is based on a two-sided 95% CI for a single proportion using the Z-test approximation, an effect size of 0.1 and an expected observed proportion of 0.90. The number of participants with caries that meet the power of 0.8 is estimated to be 35 [n ≥ (Z^2^/m^2^) p (1 - p)]. With the prevalence of caries at 35% (1.86 × 65), 65 participants without caries are needed. After considering a 20% drop out rate, the proportion that gives the largest sample size shows that at least 125 children per group will be needed. Three schools will be required in each group with a maximum of 45 children in each school.

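### The 9-month cost comparison counts treatment of decay already present at baseline but states no adjustment for baseline decay and no school-level interval, which adds avoidable noise to the cost-saving conclusion

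*Protocol article*

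**What the plan says.** The second objective carries a directional hypothesis, that the teledental pathway saves cost. The Data analysis section answers it in these terms: "a cost minimisation analysis will be undertaken to compare the costs associated with teledental versus the usual pathway of dental care over 9 months". On content it adds: "This will include both the cost of the initial screening, and any subsequent interventions occurring over the 9 months". The Outcome assessment section names the treatment items: "Dental care costs for all children include the following: restorations, restorations with crowns and extractions". It also says that the purpose is to find the cheaper alternative. None of these items is split between decay present at baseline and decay that develops later.

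Decay found at baseline is acted on. For the control pathway, the Visual dental examination section says that "children with active caries will be referred to local dental providers for further investigations". For the teledental pathway, parents receive advice on care based on the images.

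The only adjustment in the Data analysis section belongs to the DFT/dft regression: "adjusting for baseline data collected via a survey that includes tooth brushing (yes/no; frequency", followed by dental visits, age, Indigenous status, area socio-economic index, insurance and parental education. Baseline decay is not in that list. For costs, the section states a perspective, a time window and salary rates, but no covariate, interval or allowance for schools.

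The abstract describes "approximately three schools in each group with a maximum of 45 children in each school" and a standard dental examination of every child at baseline.

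**The concern.** Restorations, crowns and extractions in the 9 months after a screening will include work on teeth that were already decayed when the child was screened. That part of the cost follows the decay burden each arm started with, which neither pathway caused. With about six schools allocated, the two arms can start with clearly different burdens by chance alone. A comparison of arm costs that ignores this carries the starting difference straight into the answer to the second objective.

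At stake is the precision of the cost-saving conclusion. The Methods section says the trial should help to justify a larger one, and the Background says cost comparisons matter to those deciding on new services. An arm that looks cheaper because its schools had less decay would be poor evidence for either purpose.

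**Working it through.** **1. The plan's own figure.** The sample size is a precision calculation for one proportion, with Z = 1.96, p = 0.90 and m = 0.1:

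n = 1.96² × 0.90 × 0.10 / 0.1² = 34.57, so 35 children with caries.

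At 35% prevalence the total is 35 / 0.35 = 100, so 65 are without caries. With 20% dropout, 100 / 0.80 = 125 per group. The figures reproduce. The sentence "With the prevalence of caries at 35% (1.86 × 65), 65 participants without caries are needed" contains a slip: 1.86 × 65 = 120.9, whereas 1.86 × 35 = 65.1. The calculation serves sensitivity and specificity and says nothing about the precision of a cost difference.

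**2. Chance imbalance in baseline caries.** Inputs from the Sample size calculation section are prevalence 0.35, 125 children per arm and three schools per arm, hence 125 / 3 = 41.7 children per school. The ICC is not given, so it is an assumption and is varied.

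DE = 1 + (41.7 − 1) × ICC

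SD of the between-arm difference = √(2 × 0.35 × 0.65 / 125 × DE) = √(0.00364 × DE)

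| Assumed ICC | DE | SD (points) | SD relative to 35% | P(gap of at least 10 points) |
|---|---|---|---|---|
| 0 | 1.00 | 6.0 | 17% | 10% |
| 0.01 | 1.41 | 7.2 | 20% | 16% |
| 0.02 | 1.81 | 8.1 | 23% | 22% |
| 0.05 | 3.03 | 10.5 | 30% | 34% |
| 0.10 | 5.07 | 13.6 | 39% | 46% |

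The last column uses a normal approximation. The relative SD carries over to treatment cost only if that cost is proportional to baseline caries prevalence, which is a further assumption.

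**3. Share of treatment cost due to existing decay.** The article gives no treatment uptake and no rate of new decay. Let u be the fraction of children with baseline caries who need a costed item, let i be the fraction of all children with new treated decay, and let the cost per treated child be equal:

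share = 0.35u / (0.35u + i)

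- u = 1: i = 0.05 gives 0.35 / 0.40 = 88%; i = 0.20 gives 0.35 / 0.55 = 64%.
- u = 0.5: i = 0.05 gives 0.175 / 0.225 = 78%; i = 0.20 gives 0.175 / 0.375 = 47%.
- u = 0.3: i = 0.05 gives 0.105 / 0.155 = 68%; i = 0.20 gives 0.105 / 0.305 = 34%.

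A value of u below 1 is realistic because the caries definition is wide: "Teeth will be classified as carious if have arrested caries, caries into dentine or enamel level caries". The share is substantial throughout, but not always above half.

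**4. What adjustment could gain.** An illustrative simulation used six schools of 42 children, half of the carious children treated with a mean of two teeth each, and 10% with new decay, half of them treated. Subtracting the part explained by baseline caries reduced the SD of the treatment-cost difference, relative to mean treatment cost, as follows:

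- ICC 0.02: 31% to 24%
- ICC 0.05: 36% to 24%
- ICC 0.10: 42% to 24%

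These assumptions favour adjustment: existing decay makes up 0.35 / 0.40 = 87.5% of treatment cost, and the slope is taken as known. A smaller share would give a smaller gain.

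**5. The interval.** Six schools in two arms leave 6 − 2 = 4 degrees of freedom. The 95% multiplier is then 2.78 instead of 1.96, which is 2.78 / 1.96 = 1.42 times as wide before any inflation of the standard error.

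**The case against.** The strongest reply is that the article never says costs will be compared without adjustment. It is silent, and covariates for a secondary economic outcome are commonly left to an analysis plan, which is not shown. That stands: a reader might infer a decision not to adjust, and the text does not support it. What remains is that the same section does set out an adjusted model for DFT/dft, and that its listed covariates would miss baseline decay even if they were carried over to costs. Following the text as printed therefore gives a noisier answer than data already planned would allow.

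Second, paying for existing decay is no design error. Finding it and referring it is what each pathway does, and missed lesions or extra referrals act largely on it. Random allocation balances the burden in expectation. This is right, so a reading of systematic bias fails.

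Third, the school mechanism depends on how allocation is done. The Allocation section names the school as the unit, but also describes permuted blocks of four at each school, with lists opened as children are found eligible. If children were allocated within schools, the between-school inflation would largely vanish and the SD would lie near the 6 points of simple sampling. The abstract and the Sample size calculation section support school allocation, but the passages need to be reconciled.

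Fourth, even after adjustment much noise remains, and four degrees of freedom give a wide interval. That is true. Adjustment improves the answer but does not guarantee a decisive one.

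**Conclusion.** The point holds as a matter of precision. Treatment of baseline decay is inside the 9-month total, and neither an adjustment for it nor a school-level interval is stated. With three schools per arm, 125 children per arm and 35% prevalence, the chance SD of the baseline gap is about 7 to 14 points for assumed ICCs of 0.01 to 0.10. Of this, 6 points would arise without any clustering.

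Two stronger conclusions are tempting but not supported. One is that the cost comparison pays mostly for old decay: under the assumptions shown, the share runs from 34% to 88%, and the article gives no figures to narrow it. The other is that chance differences between schools can decide the cost-saving claim. The total also contains vehicle, staff, software and equipment costs that differ between pathways by design, and no unit costs are given, so a reversal of sign can be neither shown nor excluded.

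**What to change.** In the Data analysis section, state that 9-month cost per child will be analysed in a model containing arm and the baseline number of decayed teeth recorded at the visual examination. The covariates already listed for DFT/dft can be added as far as six schools allow. Use the visual record in both arms: the Outcome assessment section names image-based records and the control group's forms as data sources, and adjusting each arm by a different method would build in a measurement difference.

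Take the adjusted cost difference, with an interval that respects schools (about 4 degrees of freedom with six schools), as the answer to the second objective. Report screening cost and treatment cost separately, so that the part that differs by design can be told apart from the part driven by decay. Reconcile the two descriptions in the Allocation section first, because the form of the interval depends on which one applies.

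The change costs a paragraph of wording and a little more analysis. It needs no new examinations, since every child is to have the baseline examination. The price is a wider but more honest interval.
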